#### Primary outcome measures of the quality improvement strategy

The primary outcome of the quality improvement strategy is the quantity of tests ordered in relation to the instruction to either order blood tests immediately or to suggest a 4-week watchful waiting policy.

#### Secondary outcome measures

The secondary outcome measures are summarised in table 4.

**Table 4 T4:** Secondary outcome measures

Incidence of unexplained complaints in general practice
Predictive value of GPs' working hypothesis
Duration of unexplained complaints
Effect of unexplained complaints on patients' quality of life
Effect of immediate testing or watchful waiting on patients' satisfaction with care, anxiety, medical consumption and sick leave
Effect of immediate testing or watchful waiting on GPs' satisfaction, anxiety and insecurity
Effect of quality improvement strategy on GPs' knowledge about the value of blood test ordering in unexplained complaints, communication skills and attitudes
Barriers to and facilitators of GPs proposing a watchful waiting strategy
Costs of the quality improvement strategy

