### Measurements

All measurement instruments, measurement times and variables are summarised in table 3.

**Table 3 T3:** Instruments and variables.

**Instrument**	**Variables**	**Time points**					**Population**	**Method**
		**T0**	**T1**^#^	**T1.5**^#^	**T6**	**T12**		**- Provision** **- Person who completes questionnaire** **(- Comments)**

GPs' background data	Personal data	x					All GPs	- By mail
	Practice characteristics	x						- GP
	CME	x						
	Laboratory facilities available in practice	x						

Complaint registration form (for each individual type of complaint)	Symptoms	x	x				All patients	- Present in practice
	Signs	x	x					- GP
	Working hypothesis	x	x					
	Degree of unexplainedness	x	x					
	Degree of suspicion of serious pathology	x	x					
	Degree of insecurity of GP	x	x					
	Satisfaction of GP	x	x					

Patients' background data (included in patient questionnaire)	Date of birth	x	x	x	x	x	All patients	- Handed out by GP (T0, T1)
	Country of birth	x	x	x	x	x		- By mail (T1.5-T12)
	Sex	x	x	x	x	x		- Patient
	Marital status	x	x	x	x	x		
	Type of health insurance	x	x	x	x	x		
	Level of education	x	x	x	x	x		

Patient questionnaire	Intensity of complaints	x	x	x	x	x	All patients	- Handed out by GP (T0, T1)
	Course of complaints	x	x	x	x	x		- By mail (T1.5-T12)
	Satisfaction with care	x	x					- Patient
	Anxiety	x	x					
	Quality of life	x	x	x	x	x		
	- RAND 36							
	- Euroqol thermometer							
	Utilisation of health care	x	x	x	x	x		

Test ordering form	Quality of test ordering	x*	x*				All patients	- Present in practice
	Quantity of test ordering	x	x					- GP

Test result form	Test results	x*	x*				All patients	- Laboratory
								- Laboratory staff

Record examination form	Final diagnosis					x	All patients	- Practice/university
	Utilisation of health care					x		- Researcher
	Use of watchful waiting strategy					x		

		**Meeting 1**		**Meeting 2**		**Practice visit**		

Reports of small group meetings	Participation	x		x			All GPs in intervention group	- Meeting room
	Learning effects	x		x				- Researcher

Evaluation forms of small group meetings	Valuation of programme	x		x			All GPs in intervention group	- Meeting room
	Learning effects	x		x				- Researcher
	Suggestion for improvement	x		x				

GP interview in practice	Barriers and facilitators during change					x	All GPs in intervention group	- Practice
	Stages of change					x		- GP

Cost registration	Costs of development and organising of strategy	x		x		x		- University
								- Researcher

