* T0 for patients randomised to group 1, T1 for all patients but only if they revisit their GP

^# ^T1 is the time point to measure a follow-up visit by the patient 4 weeks after inclusion. If a patient does not return to the GP, a questionnaire is sent by mail after 6 weeks. This time point is indicated as T1.5.

Most questions in the questionnaires have been formulated by the research team, based on topics found in the literature. Quality of life is measured by the RAND SF36, together with the thermometer of the Euroqol questionnaire. Both are widely used and have been validated extensively.[24-26]

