#### GPs

Background data of all participating GPs are collected before the start of the patient inclusion process. Data on whether the GPs are satisfied with the consultation, whether they suspect serious pathology and whether they are certain about the diagnosis are collected from the complaint registration form. The GPs' test ordering behaviour is derived from the test ordering forms and the patient records. GPs in group 3 are asked to complete evaluation forms on process items of the quality improvement strategy. In addition, the determinants of their change processes they mentioned are audiotaped during the practice visit that is part of the quality improvement strategy.

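### After T0, patient anxiety and satisfaction are scheduled only in patients who return, and GP learning only in group 3, so the matching Table 4 effects have no as-allocated comparison

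*Protocol article*

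**What the plan says.** Table 4 (Protocol article, Secondary outcome measures) words two outcomes as causal effects of the allocated strategy:

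- for patients, an effect of testing at once or waiting on their "satisfaction with care, anxiety, medical consumption and sick leave";
- for GPs, "Effect of quality improvement strategy on GPs' knowledge about the value of blood test ordering in unexplained complaints, communication skills and attitudes".

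Table 3 (Measurements) sets out when each variable is collected. In the patient questionnaire, the rows "Satisfaction with care" and Anxiety are marked in the T0 and T1 columns and nowhere else. The footnote defines the time points: "T1 is the time point to measure a follow-up visit by the patient 4 weeks after inclusion", and "If a patient does not return to the GP, a questionnaire is sent by mail after 6 weeks". That mailed form is T1.5.

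For GPs, the reports and evaluation forms of the small-group meetings and the practice interview have as their population "All GPs in intervention group". The GPs paragraph under Measurements agrees: "GPs in group 3 are asked to complete evaluation forms on process items of the quality improvement strategy". The Control group section makes group 2 the comparator for group 3.

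Types of analysis promises an intention-to-postpone analysis, with repeated-measurement and multilevel techniques.

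**The concern.** An effect of immediate testing against watchful waiting needs a follow-up value in patients of all groups, whatever happened to them after allocation. For anxiety and satisfaction the schedule gives one only in patients who came back. Returning is decided after randomisation and depends on whether the complaint persisted. It may also depend on the arm: by week 4, patients in group 1 should have been tested once and most patients in groups 2 and 3 not at all. A comparison among returners could therefore show a difference the policy did not cause, or hide one it did.

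This matters for the policy question. The Background gives patient anxiety as one possible harm of needless testing, and research question 3 counts satisfaction among the immaterial costs of the two policies. A reader of the results would take a Table 4 effect to have the protection of randomisation.

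The GP outcome has a simpler problem. An effect of the strategy on knowledge, skills or attitudes needs the same measure in the control group, and none is listed there.

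**Working it through.** No arithmetic in the article bears on this point. The check sets the schedule against the claims.

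**Patients.** The patient questionnaire rows of Table 3, with the footnote's definitions in the column heads:

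| Item | T0 (all) | T1 (returners) | T1.5 (non-returners, by mail) | T6 (all, by mail) | T12 (all, by mail) |
|---|---|---|---|---|---|
| Satisfaction with care | x | x | – | – | – |
| Anxiety | x | x | – | – | – |
| Intensity and course of complaints | x | x | x | x | x |
| Quality of life (RAND 36, Euroqol thermometer) | x | x | x | x | x |
| Utilisation of health care | x | x | x | x | x |

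1. The other questionnaire items are marked at all five points. The two items in question are treated differently within the same instrument, so the gap is specific to them.
2. T1 and T1.5 are alternatives: a patient has one or the other. For complaints, quality of life and utilisation the two together cover everyone. For anxiety and satisfaction only the T1 half exists.
3. The Procedure section asks patients to return if the complaint has not gone within 4 weeks. Returners are therefore selected on an outcome of the trial.
4. If a proportion r returns, the share with no anxiety or satisfaction value after T0 is 1 − r. The article does not give r. It does say that most such complaints are expected to resolve by themselves, so on its own expectation the non-returners would be a large group.
5. A repeated-measurements model does not repair this. No non-returner has a later value of either item, so a model estimate for them would rest on an assumption these data cannot test.
6. T0 is different. Practices are randomised before patients enrol, and every patient receives the first questionnaire at the first consultation. If it was completed after testing or waiting had been proposed, T0 permits a comparison of the immediate reaction by assigned group in all patients. It precedes any test result and the 4-week wait, so it cannot show the effect of either.

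**GPs.** Setting Table 4 beside Table 3:

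1. No Table 3 row is called knowledge, communication skills or attitudes, in any group.
2. The nearest entries are learning effects (meeting reports and evaluation forms) and, in the practice interview, barriers, facilitators and stages of change. All are confined to group 3.
3. What is listed for all GPs is background data before inclusion starts and, per consultation, items such as satisfaction, suspicion of serious pathology and insecurity. None of these measures knowledge, skills or attitudes.
4. The number of group 2 GPs with a listed counterpart to the group 3 learning measures is therefore zero.

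**The case against.** The strongest reply is that the randomised comparison is not lost altogether, because T0 is collected in all patients after practices are allocated. That stands. A reader might infer from Table 3 that anxiety and satisfaction cannot be compared by allocation at any time; the article does not support that. The point is confined to effects after T0. The reply has its own condition, since the article does not say whether the first questionnaire was filled in before or after the consultation.

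A second reply is that nothing shows return to differ between arms: all groups receive the same instruction, and no return rates are given. This also stands, and it rules out stating a size of bias or a percentage missing as a finding. It does not rescue the comparison. Equal return rates would not make returners in the different arms alike, and the result would still not describe all patients as allocated.

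A third reply is that a journal article condenses its protocol, and Table 3 gives summary headings. This has force where a variable is simply not named. A reader might infer that sick leave, which shares the Table 4 line with anxiety, was never collected; it may sit under a broader heading or within questionnaires that are not shown, so that inference is not made here. A reader might also infer that GP knowledge and attitudes were measured in group 3 alone; strictly, Table 3 names no such measure in any group. The reply has less force for anxiety and satisfaction, which are named and given explicit time points that stop at T1.

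Finally, these are secondary outcomes. The primary outcomes, complaint course, quality of life and health care utilisation are not affected. That limits the weight of the point but does not answer it.

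**Conclusion.** The point holds in a limited form. As scheduled, the effect of immediate testing against watchful waiting on anxiety and satisfaction after T0 cannot be estimated as an as-allocated comparison in all patients. Every later value comes from patients who returned. The article lists no measure in group 2 that would make the strategy's effect on GP knowledge, skills and attitudes a controlled comparison.

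The size cannot be put as a number from the article. The conclusion assumes that Table 3 reflects what the questionnaires contained. If the T1.5 form did carry the two items, the table is wrong and the patient part of the point falls away. The matter should be corrected because it concerns causal claims that the listed data do not support, though it does not threaten the main results.

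**What to change.** Data collection ended on December 31, 2004, and the authors describe themselves as cleaning and analysing data, so items can no longer be added. The changes are to labelling and analysis:

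- Report T1 anxiety and satisfaction as descriptive in returners, by group, with the number returning in each group and no claim of an effect.
- Limit any randomised comparison of these two items to T0, stating when the form was completed relative to the consultation.
- Use the RAND 36 and the Euroqol thermometer (T1 or T1.5, then T6 and T12, all patients by assigned group) as the randomised patient-reported comparison. Say that they do not replace satisfaction with care, and that the first follow-up point combines a 4-week visit with a 6-week mailing.
- Relabel the GP learning outcome as an uncontrolled description of group 3.
- If T1.5 did carry anxiety and satisfaction, correct Table 3 instead and analyse T1 and T1.5 as one follow-up point in all patients by assigned group.

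The cost is wording in Table 4 and in the results, plus one check of the questionnaires actually mailed.

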#### Types of analysis

An intention-to-postpone analysis will be performed. Longitudinal comparisons will be made using repeated measurements techniques and multilevel analysis to correct for potential clustering of outcomes in GPs and practices. Barriers to and facilitators of change are analysed qualitatively.

#### Non-inclusion analysis

A non-inclusion analysis will be performed to check whether included patients are comparable to patients who are eligible but not included.

## Discussion

### Reasons for publishing this study design

This protocol describes an RCT which combines the generation of new clinical and epidemiological evidence to underpin guidelines on test ordering in unexplained complaints with the implementation of these guidelines. To our knowledge, this is the first RCT to integrate questions on clinical epidemiology and quality of care. The first reason for us to opt for this combination is that it meets suggestions made in the literature to evaluate the value of diagnostic tests just as rigorously as is done with treatments, namely by RCTs, and to pay attention to the implementation of evidence while generating it.[27] Secondly, both sub-studies require large numbers of participants with the same characteristics, and combining the two increases the efficient use of available resources. Apart from the advantages of the combination, however, we also need to mention one methodological disadvantage. Ideally, the evidence on which a quality improvement strategy is based should already be available at the start of development of the strategy, as it might influence its format. In the case of this study, evidence generation on one hand and the design and execution of the strategy on the other run in parallel. Evaluation at the end of the study should clarify whether the new evidence will necessitate alterations in either the diagnostic guidelines or the quality improvement strategy.

General reasons to publish the design of a study before the analyses have begun have been discussed by Godlee and De Bruijn et al.[28,29] In the case of the present study, there was an additional reason to do so. The design of the study presented here is rather complicated because, due to the nature of unexplained complaints, we had to seek methodological solutions that were not always straightforward.[22] By presenting the decisions made in designing this study, we are hoping to start a debate on proper methodology for research into unexplained complaints.
